**Methods/design:**

The study will be a pragmatic randomized controlled non-inferiority trial with two parallel groups. A total of 140 patients aged 45 years and older with knee osteoarthritis who contacted their general practitioner and have persistent knee pain (score ≥ 3 on 0–10 numerical rating scale; 0 = no knee pain) will be included.

Patients will be randomly allocated (1:1) to an injection of 40 mg triamcinolone acetonide intra-articular in the knee joint or intramuscular in the ipsilateral ventrogluteal area.

The effect of treatment will be evaluated by questionnaires at 2, 4, 8, 12, and 24 weeks after injection. The primary outcome is patients’ reported severity of knee pain measured with the pain subscale of the Knee injury and Osteoarthritis Outcome Score 4 weeks after injection. Statistical analysis will be based on both the per-protocol and the intention-to-treat principle.

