#### Follow-up measurements

Outcomes are measured at 2, 4, 8, 12 and 24 weeks after administration of the injection using digital questionnaires. Patients without an electronic mailbox will receive paper questionnaires. The primary outcome is patient reported severity of pain at 4 weeks after injection measured with the KOOS pain subscale (0–100; 0 = extreme pain). Secondary study endpoints are listed in Table 2. Patients’ perceived recovery is measured with a 7-point Likert scale that will be dichotomized in recovered (‘complete recovery’, ‘much improved’, ‘slightly improved’) and not-recovered (‘no change’, ‘slightly worse’, ‘much worse’,“worse than ever’) [18]. Percentage responders is defined by the OMERACT-OARSI criteria: High improvement (≥50%) in KOOS pain subscale or in KOOS function in daily living subscale and absolute increase ≥20 points in KOOS pain subscale or function in daily living subscale, if not then improvement in at least 2 of the 3 following domains: 1) ≥20% improvement in KOOS pain subscale and ≥ 10 points increase in KOOS pain subscale, 2) ≥20% improvement in KOOS function in daily living subscale and ≥ 10 points increase in KOOS function in daily living subscale, 3) ≥20% increase in global score and ≥ 10 points increase in global score. In this study patients’ global score will be measured with a patients’ perceived recovery score measured on a 7-point Likert scale. This domain is considered improved if a patient fills in ‘complete recovery’, ‘much improved’, or ‘slightly improved’ [38]. Two weeks after administration of the injection patients are asked to report adverse events. Also, follow-up questionnaires at all time points ask about hospitalization to monitor Serious Adverse Events. Co-interventions including medication, non-drug therapies such as physiotherapy, referrals and surgery will be measured with the modified medical consumption questionnaire of the Institute for Medical Technology Assessment (iMCQ) [39]. Experienced painfulness of injection will be registered 2 weeks after glucocorticoid injection. All data will be handled according to the Data Monitoring Plan, as drafted and approved by the funder in preparation of data collection.

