### Data analyses

Imbalance in the baseline variables of the two treatment arms might occur after randomization. This is problematic if the imbalanced variable is related to the outcome variable, as this could lead to confounding [44, 45]. In case imbalance occurs, we will adjust for relevant variables. Descriptive statistics will be used to describe patients’ and complaints characteristics at baseline. Analyses will be adjusted for variables that hamper the baseline interchangeability of groups when there are clinically relevant differences between groups of over 10%.

The primary outcome is patient reported severity of pain at 4 weeks after injection measured with the KOOS pain (0–100; 0 = extreme pain). We will use a non-inferiority design to assess if an IM gluteal injection is non-inferior to an IA knee injection with regard to this outcome. In non-inferiority comparisons intention-to-treat analysis can bias towards the null and could increase type I error; the risk of falsely claiming non-inferiority [46]. Therefore, the per-protocol analysis will be the primary analysis. Included in the per-protocol analysis will be patients who received the assigned injection and reported the KOOS pain at 4 weeks follow-up. In case a patient from the IM injection group receives an additional IA injection earlier than 6 weeks after the study injection, this will be considered as a protocol violation and the patient will be excluded from the per-protocol analysis. The reason for this is that the guideline from the Dutch College of General Practitioners recommends to leave at least 6 weeks between two consecutive injections [6]. Non-inferiority of the IM injection will also be assessed using both intention-to-treat and per-protocol analysis at 2, 8, 12 and 24 weeks follow-up and for the outcome KOOS pain. For the other outcome measures we will calculate mean differences.

We expect 10–15% of missing data (incompletely filled in paper questionnaires and loss to follow-up). We will contact the patients to pose them the missing questions again in order to minimize missing data for the primary outcome. Multiple imputations will be performed for missing values (incompletely filled in questionnaires), creating at least five imputed datasets.

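### The week-4 non-inferiority conclusion rests on the per-protocol analysis alone; intention-to-treat at week 4 is not listed and has no stated role in the conclusion

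*Protocol article*

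**What the plan says.** The Data analyses section fixes the primary outcome ("The primary outcome is patient reported severity of pain at 4 weeks after injection measured with the KOOS pain (0–100; 0 = extreme pain") and chooses the analysis set: "Therefore, the per-protocol analysis will be the primary analysis". Its reason is that ITT can bias a non-inferiority comparison towards the null and so raise the risk of a false claim.

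The PP set is defined as "patients who received the assigned injection and reported the KOOS pain at 4 weeks follow-up". One further exclusion is written, for one arm only: "In case a patient from the IM injection group receives an additional IA injection earlier than 6 weeks after the study injection" is treated as a protocol violation and removes the patient from PP.

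The only sentence in the Methods that assigns ITT to particular visits reads "Non-inferiority of the IM injection will also be assessed using both intention-to-treat and per-protocol analysis at 2, 8, 12 and 24 weeks follow-up", and it continues with a reference to the outcome KOOS pain. The Methods/design paragraph of the abstract says "Statistical analysis will be based on both the per-protocol and the intention-to-treat principle", directly after defining the week-4 outcome and without naming a visit.

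Under Procedures, the GP and the patient learn the allocation before the injection is given. Under Blinding, neither is blinded.

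**The concern.** The four secondary visits each get a non-inferiority assessment in both sets. The visit that carries the trial's claim is the one not listed for ITT. The abstract and the Data analyses section therefore differ in scope, and a reader cannot tell whether a week-4 ITT result is planned or what weight it would have.

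The article's reason for preferring PP supports including PP. It does not show that this PP set is the stricter one, because its exclusions all occur after randomisation and may depend on preference or response:

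- A patient who declines the allocated route, once it is known, leaves PP. The Strength and limitations section itself accepts that lack of blinding might bias results towards the preferred site.
- A patient with no week-4 score leaves PP. The Data analyses section expects 10-15% missing data.
- An IM patient given an additional intra-articular (IA) injection before 6 weeks leaves PP, and no matching exclusion is written for the IA arm. Such an injection plausibly marks a poor response, so the rule can favour IM. The 6-week window also runs past the week-4 outcome.

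At stake is a non-inferiority claim made on PP that the comparison of the randomised groups at the same visit does not support.

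**Working it through.** **Inputs from the article.** Sample size section: margin 7, SD 16, power 80%, alpha 5% (sidedness not stated), 65 per group, about 140 in total. Higher KOOS pain is better, so the difference is taken as IM minus IA and the margin is -7.

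**Inputs assumed, not in the article.** A fraction f of IM patients is excluded from PP, and their mean KOOS pain is d points below that of the remaining IM patients. No IA patients are excluded.

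**Step 1. Reproduce the sample size.** n per group = 2 × [16 × (z for alpha + z for power) / 7]².

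- One-sided 5%: 2 × [16 × (1.645 + 0.842) / 7]² = 64.6, rounded up to 65. This matches the article.
- One-sided 2.5%: 2 × [16 × (1.960 + 0.842) / 7]² = 82.0, rounded up to 83. This does not match.

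The main illustration therefore uses one-sided 5%.

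**Step 2. Standard error.** SE = 16 × √(2/65) = 2.807.

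**Step 3. Shift of PP relative to all IM patients.** The shift is f × d towards IM. With f = 5% and d = 10 to 20 it is 0.05 × 10 = 0.5 to 0.05 × 20 = 1.0 points, or 7-14% of the margin.

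**Step 4. Chance of a PP claim when the true difference among all randomised patients is -7.** The rate is 1 - Φ(1.645 - shift/SE).

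- No shift: 5%.
- Shift 0.5: 1 - Φ(1.645 - 0.178) = 7.1%.
- Shift 1.0: 1 - Φ(1.645 - 0.356) = 9.9%.

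**Step 5. Range over f.** Here SE = 16 × √(1/65 + 1/(65(1 - f))), which allows for the smaller IM group.

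| f | Shift (d = 10 to 20) | SE | Rate, one-sided 5% | Rate, one-sided 2.5% |
|---|---|---|---|---|
| 5% | 0.5-1.0 | 2.843 | 7.1-9.8% | 3.7-5.4% |
| 10% | 1.0-2.0 | 2.883 | 9.7-17.1% | 5.3-10.3% |
| 15% | 1.5-3.0 | 2.928 | 12.9-26.8% | 7.4-17.5% |

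**Step 6. The other direction.** If the excluded IM patients did better than the rest, the sign reverses. A shift of -0.5 gives 1 - Φ(1.645 + 0.178) = 3.4%, and -1.0 gives 1 - Φ(1.645 + 0.356) = 2.3%. PP would then be the stricter set. The article does not show which case applies.

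**Step 7. Power cost of requiring both sets.** Assume a true difference of 0 in both sets, 70 per arm in ITT and 65 of those 70 in PP. Power is Φ(7/SE - 1.645) for each set: 80.2% for PP (SE 2.807) and 82.7% for ITT (SE = 16 × √(2/70) = 2.705). The two estimates correlate at √(65/70) = 0.964. The bivariate normal probability that both succeed is 78.4%, about 2 percentage points below PP alone.

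**The case against.** **A reader might infer that the abstract and the Data analyses section contradict each other.** They do not. The abstract names no visit, so ITT at the other four visits would satisfy it literally. What stands is a difference in scope.

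**A reader might also infer that no analysis of the randomised population exists at week 4.** The article does not support that either. The sentence on ITT ends "at 2, 8, 12 and 24 weeks follow-up and for the outcome KOOS pain", and that loose ending can be read as bringing in the primary outcome. A repeated-measures mixed model fitted to the ITT set for the other visits would ordinarily yield a week-4 contrast as well. What stands is that week-4 ITT is not explicitly listed and is given no part in the conclusion.

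**A third inference is that randomised patients who are never injected must drop out of ITT,** because "Outcomes are measured at 2, 4, 8, 12 and 24 weeks after administration of the injection". The article times the questionnaires that way but does not say how uninjected patients are handled, and it does not exclude them from ITT. That is commonly left to the full protocol, so it is not part of this point.

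**PP as primary is reasoned, and the rule for combining sets is often left to an analysis plan.** The first half is fair: PP belongs in the analysis. The second half would carry more weight had the article been silent. It instead chooses the primary set, justifies it, defines it and lists the visits for ITT, so the decision rule is one that it states.

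**The size rests on assumed inputs.** This is correct. The 9.9% is the upper end for 5% excluded, with every exclusion in one arm and in IM's favour and the true difference exactly at the margin. Calling it a false-claim rate also takes the comparison of all randomised patients as the target.

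**Conclusion.** The point holds in limited form. As written, the week-4 conclusion depends on PP alone, ITT is explicitly listed only for the other four visits, and a PP claim could stand although week-4 ITT fails. PP is not shown to be the conservative set, given open allocation before injection, exclusion for a missing week-4 score, and a re-injection exclusion that applies only to the IM arm.

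The size is illustrative. If 5% of the IM arm is excluded with outcomes 10 to 20 points worse, PP moves 0.5 to 1.0 points towards IM, and the false-claim rate at a true difference of -7 goes from 5% to about 7-10% at one-sided 5%. More exclusions raise it, and exclusions of better-than-average IM patients lower it below 5%. The excluded fraction and the outcome gap are not in the article. This is a cheap improvement to the decision rule and no evidence that the result will be biased.

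**What to change.** In the Data analyses section:

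1. Add week 4 to the visits at which KOOS pain non-inferiority is assessed by ITT, and define ITT as all randomised patients, analysed as allocated.
2. State that non-inferiority is concluded only if the week-4 KOOS pain confidence limit lies above -7 in both the PP and the ITT analysis.
3. Word the abstract to match, so that both places say which sets apply at week 4.

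This takes about two sentences in the Data analyses section and one in the abstract. It needs no new data and no alpha adjustment, because requiring both sets to succeed cannot raise the chance of a claim above that of either set alone. The cost is a small loss of power, about 2 percentage points under the assumptions in the working (80.2% to 78.4%). The change should be fixed before treatment groups are revealed to the blinded analyst.

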### Sample size

For the sample size calculation, we used data from the study of Henriksen et al. that evaluated the clinical benefits of an IA glucocorticoid injection given before exercise therapy in patients with knee OA [40]. The results of the study reported a baseline standard deviation of 16 for the KOOS pain (recommended by the KOOS for sample size calculations is a standard deviation of 15). The minimal important difference (=non-inferiority margin) between both treatment groups of the patient reported outcome KOOS (0–100) was set at 7 points (effect size of 0.44) [41, 42].

For the non-inferiority of an IM gluteal glucocorticoid injection compared to an IA knee glucocorticoid injection, we will need 65 patients per group, using a power of 80%, an alpha of 5%, a non-inferior margin of 7 and a SD of 16. Taking into account a loss to follow-up of 5%, this trial needs to include (2*65) + (0.05*2*65) = ~ 140 patients. We expect a low percentage of loss to follow-up because of the relative short follow-up period of 24 weeks and our prior experience in glucocorticoid trials [18, 43].

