Linear mixed models with repeated measures will be used to calculate group differences over time for the primary outcome as this is a continuous variable. To model the covariance of repeated measures by patients, a structure will be chosen with the lowest Akaike’s information criterion. Fixed effects will be time, and time by treatment.

Linear mixed models with repeated measures will also be used for the continuous secondary outcomes: KOOS, NRS, WOMAC, ICOAP, and EQ-5D-5 L. Generalized estimating equations analyses with repeated measures will be performed for the dichotomous outcomes: patients’ perceived recovery (7 point Likert scale), and the OMERACT-OARSI responder criteria. Before generalized estimating equations analyses, multiple imputations will be performed for missing values of secondary study parameters, creating at least five imputed datasets.

When patients underwent a total knee replacement surgery, data of these patients will be included up to the date of surgery. Missing data for secondary outcome measurements will be handled similarly as missing data for the primary outcome.

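### The primary per-protocol set requires a reported week-4 KOOS pain score, which is not adherence, and the 5% inflation may not cover the missing data and per-protocol exclusions the plan itself foresees

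*Protocol article*

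**What the plan says.** All references are to the Methods of the protocol article.

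- **Data analyses, analysis set.** Per-protocol is the primary analysis, chosen because intention-to-treat could raise the risk of falsely claiming non-inferiority. Membership is defined in one sentence: "Included in the per-protocol analysis will be patients who received the assigned injection and reported the KOOS pain at 4 weeks follow-up". IM patients who get an additional IA injection within 6 weeks are also removed. Non-inferiority on KOOS pain is to be assessed at weeks 2, 8, 12 and 24 too, by both principles, and no other per-protocol definition is given.
- **Data analyses, missing data.** "We expect 10–15% of missing data (incompletely filled in paper questionnaires and loss to follow-up"). Patients will be contacted again about missing questions, and incompletely filled in questionnaires will be multiply imputed.
- **Data analyses, model.** "Linear mixed models with repeated measures will be used to calculate group differences over time for the primary outcome", with time and time-by-treatment as fixed effects. Table 2 schedules KOOS pain at baseline and at weeks 2, 4, 8, 12 and 24.
- **Sample size.** 65 per group, "using a power of 80%, an alpha of 5%, a non-inferior margin of 7 and a SD of 16". The inflation is for loss to follow-up alone: "Taking into account a loss to follow-up of 5%, this trial needs to include" about 140 patients.

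**The concern.** A per-protocol set should show what happens in patients treated as planned. Returning a questionnaire at week 4 is not part of treatment. Making it a condition of entry selects patients on a post-randomisation event tied to the primary outcome.

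Two things are at stake.

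1. **Selection.** Patients know their allocation, and the Discussion accepts that their preference for an injection site might bias results. If IM patients who did badly reply less often than others, the rule would favour IM. That is the error the per-protocol choice was meant to guard against. Non-response among IA patients who did badly would push the other way. The plan gives no information on which is more likely, so the direction is unknown.
2. **Size of the primary set.** Whoever leaves the per-protocol set, for whatever reason, reduces the number on which the 80% power rests. The inflation covers only one of those reasons.

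**Working it through.** **Set definition against model.** Take a patient who received the assigned injection, had no additional injection, and answered at weeks 2, 8, 12 and 24 but not at week 4.

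- Under the membership sentence this patient is out of the primary analysis. With no other definition given, the patient is also out of the per-protocol analyses at weeks 2, 8, 12 and 24, where the scores exist.
- Under the repeated-measures model the same patient could contribute four follow-up scores, which inform the week-4 contrast through the covariance structure.
- For a patient with a partly completed week-4 form, imputation is planned, but the text does not say whether an imputed score makes the patient one who reported it.

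**Reproducing the sample size.** Inputs from Sample size: margin 7, SD 16 (a baseline SD), power 80%, alpha 5%. Allocation is 1:1. The text does not state the true difference (taken as 0) or the sidedness of alpha. One-sided 5% is the variant that returns the stated number:

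- n per group = 2 × [16 × (1.645 + 0.842) / 7]² = 64.6, rounded up to 65, as stated.
- Inflation: 130 + 0.05 × 130 = 136.5, so 137, which the protocol rounds to about 140.

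**Loss the 140 can absorb.** 1 − 130/140 = 7.1%, from all causes together.

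**Power after loss from the per-protocol set.** Power = Φ(7 / (16 × √(2/n)) − 1.645), with n = 70 × (1 − loss):

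| Loss from 140 | Patients left | n per group | Power |
|---|---|---|---|
| Reference: 65 per group | 130 | 65 | 80.2% |
| 5% | 133 | 66.5 | 81.0% |
| 10% | 126 | 63 | 79.1% |
| 15% | 119 | 59.5 | 77.1% |

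With the noncentral t distribution the last two rows become 78.7% and 76.7%. The 10% and 15% rows assume that all the expected missing data fall on the week-4 outcome and lead to exclusion. They make no deduction for patients who did not receive the assigned injection or who had an early additional injection. The article gives no rate for either, so I put no figure on them; any such exclusion lowers the numbers further.

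**The case against.** Several points on the other side are sound.

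- **A reader might infer that 5% and 10–15% contradict each other.** They do not strictly. The 10–15% combines incomplete questionnaires with loss to follow-up, no split is given, and it is not tied to week 4. A 5% loss can sit inside it. The 5% also refers to 24 weeks, so loss by week 4 can only be equal or lower.
- **A reader might infer that the primary analysis will miss 65 per group and 80% power.** The documents support only that it may. Patients with missing answers are to be contacted again, and incomplete forms are to be imputed, so subtracting the whole 10–15% is the worst reading of that figure. Even then the shortfall is about 1 to 3 points. Baseline adjustment or the repeated-measures model could recover some of it.
- **A reader might quote a much lower power by taking one-sided 2.5%.** At that level 65 per group has only about 70% power with nothing missing. That is a separate question about the unstated sidedness of alpha and does not belong to this point.
- **A reader might call the primary analysis complete-case throughout.** The label fits patients with no week-4 report. It does not clearly fit partly completed forms.
- **Requiring the primary measurement for per-protocol membership is partly a matter of convention, and an intention-to-treat analysis is also planned.** True, but that analysis is not the primary one. The convention also fits poorly with a model chosen to use all time points.

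What remains is that the membership rule conditions on an observed outcome, that its link to imputation and the mixed model is unclear, and that the sample size has no explicit allowance for the treatment-related exclusions.

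**Conclusion.** The definition point holds as written in the article: it is a stated rule, not a detail left to an unseen analysis plan. It discards usable data from adherent patients and adds selection on response, of unknown direction and size.

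The sample-size point holds conditionally. Above 7.1% total loss from the per-protocol set, fewer than 65 per group remain. If all of the expected 10–15% fell on week 4, there would be 63 to 59.5 per group and power of about 79% to 77%, before other per-protocol exclusions. This rests on one-sided 5%, a true difference of 0, SD 16 and an unadjusted comparison. The shortfall is small and does not by itself threaten the trial. The change is worth making mainly because the primary non-inferiority claim depends on this set and the correction is cheap.

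**What to change.** 1. In Data analyses, define per-protocol membership by receipt of the assigned injection and the protocol-violation rule already in the plan. Delete the condition that KOOS pain was reported at week 4. The re-injection rule itself is left unchanged here.
2. Include every such patient with any post-baseline KOOS pain score in the mixed model, and take the week-4 contrast from it. State how imputed item-level data enter this analysis.
3. Add a sensitivity analysis that shifts missing week-4 scores unfavourably for IM (downwards in the IM group, since 0 is extreme pain) in steps up to the 7-point margin.
4. In Sample size, say how the 5% relates to the 10–15% and to the per-protocol exclusions. Restate power as about 77–79% if all missingness falls on week 4. Do not simply relabel the 10–15% as loss to follow-up.

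No extra patients should be enrolled; the Discussion reports that recruitment has ended. The costs are wording, slightly more analysis work, reliance on a missing-at-random assumption for patients without a week-4 score (which step 3 probes), and a slightly less favourable stated power.

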### Blinding

Due to the pragmatic nature of this trial, the patient and the GP are not blinded for treatment allocation. The researcher involved in data analysis will be blinded for treatment allocation.

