***Secondary outcome measures***							
Adverse events			x				
Hospitalization			x	x	x	x	x
Co-interventions (iMCQ)			x	x	x	x	x
Medication use for knee OA	x		x	x	x	x	x
Re-injection with glucocorticoid					x	x	x
KOOS stiffness	x		x	x	x	x	x
KOOS function in daily living	x		x	x	x	x	x
KOOS sports and recreation	x		x	x	x	x	x
KOOS QoL	x		x	x	x	x	x
ICOAP	x		x	x	x	x	x
OMERACT OARSI responder criteria			x	x	x	x	x
Knee pain over past week (NRS)	x	x	x	x	x	x	x
Perceived recovery (Likert scale)			x	x	x	x	x
Knee complaint characteristics	x		x	x	x	x	x
Health related QoL	x						

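### The primary per-protocol set drops early re-injected patients from the IM arm only and up to week 6, so valid week-4 IM scores can be removed because of later events

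*Protocol article*

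**What the plan says.** All of the following is in the protocol article, Data analyses section.

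- **Endpoint:** "The primary outcome is patient reported severity of pain at 4 weeks after injection measured with the KOOS pain (0–100; 0 = extreme pain").
- **Primary analysis set:** "Therefore, the per-protocol analysis will be the primary analysis". The reason given is that intention-to-treat can raise the risk of a false non-inferiority claim.
- **Entry, same for both arms:** "Included in the per-protocol analysis will be patients who received the assigned injection and reported the KOOS pain at 4 weeks follow-up".
- **Further exclusion, IM arm only:** "In case a patient from the IM injection group receives an additional IA injection earlier than 6 weeks after the study injection". The plan treats such a patient as a violator and takes them out of the per-protocol set.
- **Reason for that exclusion:** the Dutch general practice guideline "recommends to leave at least 6 weeks between two consecutive injections".

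Elsewhere, the Blinding section leaves patients and GPs unblinded, and the Intervention section allows co-interventions. The Abstract says the analysis will follow both the per-protocol and the intention-to-treat principle.

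**The concern.** Two features of the exclusion do not fit its purpose.

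1. **It covers one arm.** The guideline interval concerns any two consecutive injections. An IA patient re-injected before 6 weeks departs from it just as an IM patient does, yet the rule removes only the IM patient.
2. **Its window outlasts the endpoint.** An injection in week 5 cannot affect a score recorded at week 4. For an IM patient injected between the week-4 questionnaire and week 6, the rule deletes a valid primary outcome because of something that happened later.

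In an open-label trial, an early extra IA injection most plausibly follows a poor response. Removing such patients from the experimental arm alone raises its mean. The per-protocol set was chosen to guard against a false claim of non-inferiority, and for weeks 4 to 6 this rule makes that error more likely.

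**Working it through.** **Inputs from the Sample size section:** margin 7 KOOS points, SD 16, power 80%, alpha 5% (sidedness not stated), 65 per group.

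**The plan's own figure.** n per group = 2 × 16² × (1.645 + 0.842)² / 7² = 64.6, so 65. This matches the plan. A one-sided 2.5% test would need 83, so the stated 5% is one-sided and is used that way below.

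**Inputs that must be assumed.** The protocol gives neither a re-injection rate nor the scores of re-injected patients. Let f be the share of the IM arm excluded and g the number of points by which these patients score below the retained IM patients at week 4. Assume f = 3–10% (about 2 to 6.5 of 65 patients) and g = 10–20.

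**Bias.** The full-arm mean equals the retained mean minus f × g, so exclusion raises the IM mean by f × g:
- low end: 0.03 × 10 = 0.3 points (0.3/7 = 4% of the margin)
- high end: 0.10 × 20 = 2.0 points (2.0/7 = 29% of the margin)

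**False non-inferiority rate when IM is truly 7 points worse.** This treats the test as a simple comparison of two means. SE = 16 × √(2/65) = 2.807, and rate = 1 − Φ(1.645 − bias/2.807).

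| Bias (points) | Rate |
|---|---|
| 0 | 5.0% |
| 0.3 | 6.2% |
| 0.75 | 8.4% |
| 1.0 | 9.9% |
| 2.0 | 17.6% |

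Allowing for the smaller IM arm changes little. At f = 10%, SE = 16 × √(1/65 + 1/58.5) = 2.884, and a bias of 2.0 gives 17.1%.

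**Rare events.** With one excluded patient, f = 1/65 = 1.5%. The bias is then 0.15–0.31 points and the rate 5.6–6.2%. With none, there is no bias.

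**Simulation of the week 4–6 window.** In 40,000 runs at a true difference of −7, the chance of re-injection after week 4 rose as the week-4 score fell, by the same function in both arms. Excluded IM patients scored about 19–21 points below retained ones.

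| IM re-injection rate | Scores kept | IM-only exclusion | Exclusion in both arms |
|---|---|---|---|
| 5% | 4.9% | 10.1% | 6.6% |
| 10% | 4.9% | 17.2% | 8.2% |
| 15% | 5.0% | 25.5% | 9.5% |

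Applying the exclusion to both arms reduces the error but does not remove it. Keeping the week-4 scores of patients re-injected later restores the nominal rate.

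**The case against.** **Before week 4 the rule has some logic.** An IM patient given an IA injection before the week-4 assessment has received the comparator, so keeping that score could itself favour IM. A second IA injection in the IA arm is not a crossover. A reader might infer that the whole rule biases the trial towards non-inferiority. The documents support that only for the window from the week-4 assessment to week 6. The crossover argument stands for earlier injections, although it is not the reason the protocol gives, and it cannot justify exclusions after week 4.

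**Intention-to-treat is also planned.** It keeps every re-injected patient, so a per-protocol result driven by this rule should show up as a disagreement. This mitigates the problem without curing it: per-protocol is primary, and the Data analyses section names intention-to-treat only for weeks 2, 8, 12 and 24.

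**The numbers may be tiny.** The guideline interval itself discourages early re-injection. This stands, and it is why the size is given as a range that reaches almost to zero.

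**Further readings that a reader might infer and that do not hold:**
- That this is the only exclusion arising after injection. The need for a reported week-4 score is another, and it applies to both arms.
- That an arm-specific rule cannot coexist with the statement "The researcher involved in data analysis will be blinded for treatment allocation". Someone else can flag set membership before analysis.
- That early injections go unrecorded because Table 2 lists "Re-injection with glucocorticoid" only from week 8. The medical consumption questionnaire runs at weeks 2 and 4, and the look-back period of the week-8 item is not stated.

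**Conclusion.** The rule is wrong as written. It applies to one arm a reason that holds for both, and it lets events after the endpoint decide who counts in the primary analysis.

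For re-injections between the week-4 assessment and week 6 the bias favours non-inferiority, provided that re-injected patients have worse week-4 pain than the rest. For earlier injections the fault is the missing IA-arm rule, and the direction of bias is unclear.

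Under the assumed ranges (3–10% excluded, 10–20 points worse), the shift is 0.3 to 2.0 points on a 7-point margin, and the one-sided false non-inferiority rate is about 6% to 18% instead of 5%. These figures illustrate and do not predict: the documents give no re-injection rate, and with very few early re-injections the effect is negligible.

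**What to change.** For the week-4 per-protocol analysis:

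1. Apply one rule to both arms. Count as a violation only an additional glucocorticoid injection given before the week-4 KOOS assessment.
2. Keep the week-4 scores of patients re-injected after that assessment.
3. Excluding pre-week-4 re-injections still conditions on response. Add a sensitivity analysis that retains these patients with an unfavourable week-4 value, for example their baseline score.
4. Report the week-4 intention-to-treat result beside the per-protocol result.

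Identify early re-injections from data already collected: the medical consumption questionnaire, the re-injection item and GP records. Recruitment ended on 11 February 2020, so a new item on the week-2 and week-4 questionnaires would come largely too late and is not needed.

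The cost is a short change to the analysis text and slightly more analysis work, with no extra patients. The change should be recorded before the week-4 comparison is run. It concerns membership of the analysis set only, not whether or when a re-injection may be given.
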